### Sample size {14}

The most important analysis in the evaluation addresses the effect of the intervention on the primary outcome, i.e. the number of hospital days. As mentioned above, intervention and waiting control group will be compared with regard to the change scores of hospital days. These change scores will be computed by subtracting numbers of hospital stays 1 year before intervention start from numbers of hospital stays 1 year before the intervention end. The comparison of change scores will be performed using a *t*-test for independent samples. The sample size has been determined with regard to this test. The basic demand was that the test should be able to detect an effect of size 0.2 with a significance level of 0.05 and a power of 0.8. An effect size of 0.2 is a small effect according to Cohen [39]. However, unpublished analyses of our own with numbers of hospital days indicate that the standard deviation of change scores of hospital days will be between 5 and 10. In this case, an effect size of 0.2 would correspond to differences of one to two hospital days. Even a difference of only one day would mean a substantial difference in costs.

Further conditions presupposed for determining the sample are:
Two percent of the included persons could die during the intervention period or withdraw their consent for their data to be used.There could be a dropout rate of 15% in the intervention group and 20% in the waiting control group. The reason for this assumption is that up to 50% of the sample might consist of persons who are not ensured at AOK RH or BARMER. For these persons, the numbers of hospital days will not be provided directly by the health insurance companies. Instead, the patients will have to request the data from their health insurance companies and then transfer them to the project team. Several patients will not do this, with patients in the waiting control group being more likely not to do this. Within this sub-sample, a dropout rate of 30% in the intervention group and 40% in the waiting control group seems realistic. This would correspond to dropout rates of 15% and 20% in the total sample.The allocation ratio of intervention to control is 6:7.The sample size should be divisible by 13 because of the allocation ratio.

All these considerations imply a sample size of 1001.

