## Assignment of interventions: blinding

### Who will be blinded {17a}

Nobody will be blinded. This also applies to those persons who perform the central analyses for evaluation, because a reasonable blinding for these persons would not be feasible. For the primary outcome variable, this will be impossible because there will be more data sets for the waiting control group than for the intervention group. For this reason, the data analysts could identify the groups based on the numbers of data sets in both groups. Moreover, in addition to the intention-to-treat analysis, the data analysts will also perform a per-protocol analysis. For this analysis, the data sets of those members of the intervention group who have actually not participated in the intervention would have to be removed, whereas there would be no change for the waiting control group. For this reason, even if somebody other than the data analysts would prepare the data for the intention-to-treat and the per-protocol analysis, the data analysts could identify the study conditions by comparing the data sets for intention-to-treat and the per-protocol analysis. For the secondary outcome variables, blinding with regard to study conditions will be impossible, because the data analysts will also perform a process evaluation with data only from the intervention group and because data from the baseline survey will also be applied for this process evaluation.

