## Statistical methods

### Statistical methods for primary and secondary outcomes {20a}

To test the effect of the intervention on the primary outcome (i.e. on number of hospital days), the number of hospital days directly before the start of the intervention and the number of hospital days directly before the end of the intervention will be determined. The differences between these numbers will be computed, and the intervention and control groups will be compared with regard to these differences using a *t*-test for independent samples.

As outlined above (see the ‘Objectives {7}’ section), the effect of the intervention on the number of hospital days is assumed to be mediated by several different variables. Each step of the mediation will take some time. For this reason, there may well be no effect on the primary outcome although effects on the preceding variables are already identifiable. Such a pattern of results would also indicate an effect of the intervention. Consequently, if there is no statistically significant effect for the primary outcome, the pattern for the secondary outcomes will be applied in order to decide the effectiveness of the intervention. For this purpose, all secondary variables will be z-transformed and poled so that higher numbers mean better outcomes in all variables. All variables transformed in this way will be subjected to a two-factorial analysis of variance with the variables as a within-subjects factor and the study condition as a between-subjects factor. The intervention will be judged as effective if there is a statistically significant effect in favour of the intervention group. To judge whether the secondary outcomes actually determine the primary outcome, the relationships between secondary outcomes and primary outcome will be analysed using a cross-lagged panel approach with data from baseline and end surveys as predictors and the number of hospital days for the corresponding time intervals as criteria.

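### A non-significant primary test can be replaced by a second test on unblinded self-reports, with no alpha allocated, so the chance of a false verdict of effectiveness rises from 2.5% to about 4.9%

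*Protocol article*

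**What the plan says.** Objectives {7} gives one primary hypothesis: the programme reduces hospital days. Sample size {14} builds the trial on a single independent-samples t-test of the change in hospital days, which should be able to "detect an effect of size 0.2 with a significance level of 0.05 and a power of 0.8". The article names no other significance level.

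Statistical methods for primary and secondary outcomes {20a} first describes that t-test. It then argues that effects travel through several mediating steps and need time, so earlier links may respond before hospital days do. From this it draws a decision rule: "if there is no statistically significant effect for the primary outcome, the pattern for the secondary outcomes will be applied in order to decide" on effectiveness. All secondary variables are z-transformed, aligned so that higher is better, and analysed in a two-factor ANOVA with variable as the within-subjects factor and study condition as the between-subjects factor. The criterion is: "The intervention will be judged as effective if there is a statistically significant effect in favour of the intervention group". The section also plans a cross-lagged panel analysis of whether the secondary outcomes drive the primary one, but the verdict does not depend on its result.

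Outcomes {12} lists 11 secondary variables. Objectives {7} places eight of them on the psychological level, two on the behavioural level and one on the physical level. According to Plans for assessment and collection of outcomes {18a}, all are collected by postal questionnaire. Under Who will be blinded {17a} the protocol states: "Nobody will be blinded".

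**The concern.** There are two routes to one verdict. The first is a significant hospital-days test. The second opens when the first has failed and uses a different endpoint. No alpha is reserved for it, so the combined rule is more permissive than the single test on which the trial was sized.

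The routes also differ in the kind of evidence they use. Hospital days come from insurance records. The fallback rests on answers from participants who know their allocation, compared with a group waiting for the programme. Eight of its 11 equally weighted variables are psychological: four intention or perceived-control items, self-efficacy, loneliness, depression and anxiety. It could therefore succeed without a change in hospital days, self-reported physical health or behaviour.

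At stake is the trial's headline conclusion. The Discussion in the abstract says the programme may enter the disease management programmes if it proves effective, and the rule in {20a} defines when that word may be used.

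**Working it through.** **Inputs**
- Effect size 0.2, significance level 0.05, power 0.8: Sample size {14}. Sidedness is not stated.
- "The allocation ratio of intervention to control is 6:7", which at N = 1001 gives 462 and 539.
- Losses: "There could be a dropout rate of 15% in the intervention group and 20% in the waiting control group"; also "Two percent of the included persons could die during the intervention period or withdraw their consent for their data to be used".
- Total sample size 1001, divisible by 13: Sample size {14}.
- Level of the fallback ANOVA: not stated; two-sided 0.05 is **assumed**.
- Correlation between the two test statistics: not stated; a range is shown.

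**Step 1. Reproduce the plan's sample size.**
- Evaluable intervention: 462 × 0.98 × 0.85 = 384.8.
- Evaluable control: 539 × 0.98 × 0.80 = 422.6.
- Noncentrality: 0.2 × √(384.8 × 422.6 / 807.4) = 2.84.
- Power at two-sided 0.05 (noncentral t): 80.9%.

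The smallest multiple of 13 that reaches 80% is 988 (80.4%); the stated 1001 is the next multiple. A one-sided 0.05 test would need only 780. The plan's 0.05 is therefore best read as two-sided, with 2.5% in the favourable tail.

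**Step 2. Chance of a false verdict of effectiveness, both nulls true.**
The verdict requires a favourable significant primary result, or a non-significant primary result followed by a favourable significant ANOVA. If the tests are independent:

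P = 0.025 + 0.95 × 0.025 = 0.04875, about 4.9%.

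A significantly adverse primary result does not open the fallback, hence 0.95 and not 0.975. If the fallback opened after any primary result that was not significantly favourable, the figure would be 1 − 0.975² = 4.94%, practically the same.

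**Step 3. Chance of any significant result in either direction.**
If independent: 1 − 0.95² = 9.75%, against 5% for one test.

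**Step 4. Dependence on the correlation (bivariate normal).**

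| Correlation | False verdict of effectiveness (single test 2.5%) | Any significant result (single test 5%) |
|---|---|---|
| 0 | 4.9% | 9.75% |
| 0.2 | 4.8% | 9.6% |
| 0.5 | 4.5% | 9.1% |
| 0.7 | 4.2% | 8.4% |
| 0.9 | 3.5% | 7.0% |

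**Step 5. Primary power at N = 1001 under possible remedies.**
- Primary test alone at 0.05: 80.9%, unchanged.
- Split 0.04 / 0.01: Φ(2.84 − 2.05), about 78%. False verdict if independent: 0.02 + 0.96 × 0.005 = 2.48%.
- Split 0.025 / 0.025: 72.3%; 80% power would need N = 1196. False verdict if independent: 0.0125 + 0.975 × 0.0125 = 2.47%.

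**The case against.** The protocol gives a reason for the fallback. If the programme acts through attitudes, behaviour and physical health, hospital days may respond last, and a trial limited to 18 months could miss a real benefit. The fallback does not claim that hospital days fell, and it cannot override a significantly adverse primary result. The cross-lagged analysis shows that the authors saw the need to test the mediation link. The lack of blinding is stated openly. All this is fair, and it is a good reason to report the secondary outcomes prominently. It does not justify issuing the same verdict after the primary test has failed, with no alpha set aside and without making that verdict depend on the mediation analysis.

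Three stronger readings are tempting, and the document does not support them:

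- *The stated 5% error rate is doubled.* The 9.75% includes significant results against the intervention, and those cannot yield a verdict of effectiveness. For the verdict itself the rate stays just under 5%. The near-doubling is against the 2.5% favourable tail, a figure implied by a two-sided test but not printed in the article.
- *The rule invalidates the test of the primary hypothesis.* It does not. The t-test on hospital days keeps its own level whatever happens afterwards.
- *The ANOVA criterion could mean the interaction.* The text does not name the effect. But with all variables aligned in one direction and an effect required to favour one group, only the main effect of study condition fits. A clarifying phrase is enough.

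**Conclusion.** The concern holds for the verdict of effectiveness. The rule in {20a} raises its false-positive rate from 2.5% to about 4.9% with independent tests and about 4.5% at correlation 0.5, roughly 1.8 to 1.95 times the single-test rate. Above a correlation of about 0.7 the inflation is clearly smaller. The chance of any significant result in either direction rises from 5% to 9.75% if the tests are independent.

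These figures assume two-sided 0.05 for both tests; for the primary this is supported by the reproduced sample size, for the ANOVA it is an inference. They cover chance error only. Bias from unblinded self-report would add to the second route by an amount the article does not allow one to estimate. The midterm analysis, which uses the same statistics, is not counted.

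This is not a detail left to an analysis plan. The article itself states the rule, and the rule governs the main conclusion.

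**What to change.** State in {20a} that effectiveness is concluded only from the hospital-days t-test at two-sided 0.05. Describe the secondary-outcome ANOVA as supportive evidence of mechanism that cannot turn a non-significant primary result into a verdict of effectiveness, and name the main effect of study condition as its test. N = 1001 and about 81% power are unchanged.

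If the sponsor wants to keep a second route, alpha must be split in advance and the primary power restated: about 78% with 0.04 / 0.01, about 72% with 0.025 / 0.025. Both fall below the protocol's own 0.8, and the protocol's Discussion already warns that 1001 may not be reached. The primary-only rule is therefore the better choice.

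The change is one of wording, but it alters a decision rule in a trial that is already recruiting. Under the protocol's section on amendments {25} it would go to the ethics committee and then to the registry.

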### Methods in analysis to handle protocol non-adherence and any statistical methods to handle missing data {20c}

In general, participants assigned to the intervention group will be free to avail themselves of the different intervention components or not. The extent to which they do so will be documented, and the relationship of the extent of such use to changes in primary and secondary outcomes will be analysed.

Missing data are only expected in the case of questionnaire data, i.e. for the secondary outcome variables. For the secondary outcome variables that are based on sum scores, missing values will be imputed by the means of those items belonging to the respective variable for which the participant has provided data. A participant who has no baseline value for a specific secondary outcome variable will be excluded from the analyses that refer to that particular variable. However, this participant will be included in all analyses that refer to the variables for which this participant has a value. An intention to treat analysis will be performed for all participants who have a baseline value. In this intention to treat analysis, missing end values will be imputed by taking into consideration the natural development that can be expected for the respective variable for the duration of the intervention. This natural development will be estimated by computing the differences between end and baseline values of the completers in the waiting control group. Accordingly, a missing end value for a particular variable will be estimated by adding the corresponding difference estimated from completers in the waiting control group to the baseline value. Should the resulting value exceed the measurement range of the respective variable, the missing value will be imputed by the range boundary that has been exceeded.

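### In its classical form, the joint ANOVA on the 11 secondary variables drops anyone lacking one baseline value, and the missing-data rule does not settle whether such a person belongs in it

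*Protocol article*

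**What the plan says.** All places are in the protocol article.

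- **The joint test.** Section {20a} z-transforms all secondary variables, aligns their direction, and continues: "All variables transformed in this way will be subjected to a two-factorial analysis of variance with the variables as a within-subjects factor". Study condition is the between-subjects factor. A significant result favouring the intervention group means the programme is judged effective. The test has this role only when hospital days show no significant effect.
- **The variables.** Objectives {7} and Outcomes {12} list 11: one for physical health, two for behaviour and eight psychological. Sections 12.2 and 12.4 set the metric as change from baseline, so a variable without a baseline value has no change score.
- **Missing baseline values.** Section {20c} states: "A participant who has no baseline value for a specific secondary outcome variable will be excluded". It limits this exclusion to analyses concerning that variable, and adds that "this participant will be included in all analyses that refer to the variables for which this participant has a value".
- **Imputation.** Section {20c} fills missing items of sum-score variables with the person's own item mean. It fills missing end values from the baseline value plus the mean change of control-group completers. Nothing fills a baseline value that is missing altogether.

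**The concern.** A classical within-subjects ANOVA needs a value at every level of the within-subjects factor. Someone with ten usable variables and one missing therefore leaves the test entirely. Section {20c} handles missing baseline values one variable at a time and does not say what happens in an analysis that uses all the variables at once.

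This test can carry the trial's conclusion. An open analysis set in it leaves a choice to analysts who, under Who will be blinded {17a}, know the groups. If the gap is resolved by complete-case deletion, usable data are discarded and precision falls. The same question returns at the midterm analysis {21b} and in the subgroup analyses {20b}, which reuse the same methods.

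**Working it through.** **1. The plan's own figure.** Sample size {14} gives 1001 for the primary *t*-test, which should "detect an effect of size 0.2 with a significance level of 0.05 and a power of 0.8". The inputs are "The allocation ratio of intervention to control is 6:7" (462 and 539 of 1001), 2% loss through death or withdrawn consent, and 15% and 20% dropout.

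- Intervention: 462 × 0.98 × 0.85 = 384.8
- Control: 539 × 0.98 × 0.80 = 422.6
- Two-sided power (noncentral *t*): 0.809

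The smallest multiple of 13 reaching 80% is 988 (power 0.804), so 1001 reproduces. It concerns hospital days only. No calculation is given for the joint ANOVA.

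**2. Which gaps remain after the planned imputation.** Only a variable with no usable baseline value causes loss. There are two documented routes:

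- Section 12.1 measures intention and perceived control for physical activity with one item each. If that item is blank, there is no other item to average.
- Data management {19} sets impossible values of the modified activity questionnaire to missing.

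**3. Share lost if all 11 baseline values are required.** The rate *p* per variable is not in the documents; 1%, 2% and 5% are assumed. If missingness is independent, the loss is 1 − (1 − *p*)^11. If it is fully shared, the loss is *p*. In between, each variable is taken as missing when a latent normal score, equally correlated across the 11, falls below its *p*-quantile (simulated, 200,000 draws).

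| *p* (assumed) | Independent | Latent correlation 0.5 | Latent correlation 0.8 | Fully shared |
|---|---|---|---|---|
| 1% | 10.5% | 7.2% | 4.1% | 1% |
| 2% | 19.9% | 12.7% | 7.5% | 2% |
| 5% | 43.1% | 25.8% | 15.8% | 5% |

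If only the four intention and perceived-control measures are affected, independently and with each a single item (an assumption for the two nutrition measures), the loss is 1 − (1 − *p*)^4 = 3.9%, 7.8% or 18.5%.

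**4. Power in the independent worst case.** With complete data, the ANOVA's between-subjects effect is a *t*-test on each person's mean z-score. Take *d* = 0.2 for that mean, which is an assumption because the protocol sets no effect size for this test. Start from all 1001, which supposes that every baseline questionnaire is returned and end values are imputed as planned. The noncentrality is *d* × √(n₁n₂/(n₁ + n₂)) = 0.2 × √(462 × 539/1001) = 3.15, multiplied by √(share kept).

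| *p* (assumed) | Kept of 1001 | Power |
|---|---|---|
| 0% | 1001 | 0.883 |
| 1% | 896 | 0.847 |
| 2% | 802 | 0.805 |
| 5% | 569 | 0.661 |

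**5. The two sentences of {20c} applied to one person.** Someone lacks baseline loneliness and has the other ten variables. The joint ANOVA concerns loneliness, so the exclusion sentence removes this person. It also concerns the ten variables that are present, so the inclusion sentence keeps this person. The text does not rank the two.

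**The case against.** **The rules can be read together.** The joint ANOVA refers to every variable, so the exclusion sentence could simply govern it, leaving the inclusion sentence for other analyses. This stands. A reader might infer a flat contradiction between {20a} and {20c}, but complete-case ANOVA is compatible with the exclusion sentence. What remains is that the inclusion sentence is not limited in this way, and that the harmonious reading still discards people with usable data from the deciding test.

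**A large loss is not shown.** A reader might infer that much of the sample will be lost. The documents do not support that. They give no baseline missing rate, and items and end values are imputed. Assignment is withheld until the baseline questionnaire is returned {16b}, and non-responders to questionnaires receive repeat requests {18b}. Independence is the worst of the patterns examined. The repeat requests and the withheld assignment secure a returned form, however, not a complete one.

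**The power base.** It is tempting to start from the 81% of the sample-size calculation. That figure includes the 15% and 20% dropout, which {14} derives from patients who must request hospital data from their own insurer. It is not questionnaire dropout.

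**Selective loss.** A reader might infer that the verdict would tilt towards people with higher health literacy, away from those the programme is for. No document says who leaves scales blank. Only the telephone coaching is restricted to low literacy or activation; eligibility {10} is not.

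**Left to the analysis plan.** The fitting procedure often is, and {20a} does not use the word classical. If an unseen plan specifies an available-data model, the point is closed. But the protocol itself fixes both the form of the test and the missing-data rule, and the ordinary reading of that form is complete-case.

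**Conclusion.** The point holds as a poorly fixed analysis set for a test that can decide effectiveness. Read in the ordinary way, {20a} drops people who lack one baseline value, and {20c} does not settle whether that is intended.

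Its size cannot be fixed from the documents. For per-variable rates of 1% to 2%, the loss lies between 1% and about 20%, depending on how strongly gaps cluster within people. At 5% it lies between 5% and 43%. At 1% or 2%, power stays above 80% even under independence, given an assumed *d* of 0.2 and all 1001 participants. Both assumptions may be generous: Discussion concedes that 1001 may not be reached, and no effect size is set for this test. The matter bears on the trial's conclusion only if the primary test is not significant. It is worth correcting because a method that keeps the usable data is readily available.

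**What to change.** In {20a}, replace the two-factorial ANOVA with a linear mixed model on all available participant-by-variable z-scored changes, with condition and variable as factors and a participant-level covariance. Name the main effect of condition as the deciding test. In {20c}, state that the inclusion sentence governs this joint analysis, so that a person contributes every variable for which a baseline value exists.

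With complete data and a balanced model, this main effect matches the ANOVA's between-subjects test, so nothing is given up. Comparing each participant's mean over the available z-scores is a simpler alternative. It is not equivalent when data are incomplete, because it generally weights participants and variables differently. If it is chosen, the text should say so.

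The cost is analysis wording and a different software procedure. No additional data are needed.

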**Discussion:**

If the intervention proves effective, it may be included into the DMPs for T2DM and CHD.

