## Objectives {7}

### Primary hypothesis

P-SUP reduces the number of hospital days.

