#### 12.4 Time points

Hospital days will be sourced from the register data of the health insurance companies. These data are updated continuously. The collaborating health insurance companies will provide these data for evaluation after the intervention retrospectively to the point in time 1 year prior to the start of the intervention. The change scores for hospital days will be computed by subtracting the number of hospital days in the year directly before intervention start from the number of hospital days in the year directly before the end of the regular intervention, i.e. directly before month 18 after intervention start. Data for the secondary outcomes will be collected via a questionnaire (1) at enrolment (baseline survey), (2) 9 months after the start of the intervention (midterm survey), (3) 18 months after the start of the intervention (end survey) and (4) 27 months after the start of the intervention (follow-up survey). The baseline survey will be performed before the study participants have been informed about their assignment to one of the two study conditions. For the questionnaire variables, the core evaluation of the intervention will be based on the change scores between the values of the baseline survey and the values of the end survey, i.e. the survey at month 18 after intervention start.

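### After a non-significant hospital-day result, a significant ANOVA on self-reports alone earns the verdict 'effective', and the planned analysis of their link to hospital days has no stated bearing on it

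*Protocol article*

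**What the plan says.** All references are to the protocol article.

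- **Primary hypothesis** (Objectives {7}): "P-SUP reduces the number of hospital days".
- **Trigger of the fallback** (Statistical methods {20a}): "if there is no statistically significant effect for the primary outcome, the pattern for the secondary outcomes will be applied in order to decide" whether the intervention is effective.
- **Rationale** (same section): the effect on hospital days is assumed to run through the secondary variables. "Each step of the mediation will take some time", so "there may well be no effect on the primary outcome although effects on the preceding variables are already identifiable".
- **Verdict rule** (same section): the secondary variables are z-transformed, aligned in direction and entered in a two-factor ANOVA. Then: "The intervention will be judged as effective if there is a statistically significant effect in favour of the intervention group". No further condition is given.
- **Analysis of the link** (same section, next sentence): "To judge whether the secondary outcomes actually determine the primary outcome, the relationships between secondary outcomes and primary outcome will be analysed" by a cross-lagged panel approach. Nothing is said about what follows from its result.
- **Nature of the secondary outcomes** (Outcomes {12}; Blinding {17a}): all 11 come from participant questionnaires, and nobody is blinded.
- **Use of the verdict** (Abstract, Discussion): "If the intervention proves effective, it may be included into the DMPs for T2DM and CHD".

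**The concern.** The fallback lets one set of outcomes stand in for another. Its stated justification is a premise, namely that the self-reports lie on the causal path to hospital days and the effect on hospital days is merely late. The plan schedules an analysis of part of that premise and then leaves it out of the decision. Whether the cross-lagged paths are strong, weak or absent, the verdict after a significant ANOVA is the same.

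What is at stake is the meaning of the trial's headline word. Hospital days were chosen as the primary outcome because they are a major cost factor (Outcomes, 12.5), and effectiveness is what may open the way into the disease management programmes. A reader of the result could not tell from the word alone whether hospital use fell or whether unblinded participants gave somewhat better questionnaire answers.

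**Working it through.** **1. The decision rule, laid out**

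| Hospital-day test | ANOVA on self-reports | Cross-lagged link | Verdict as written |
|---|---|---|---|
| not significant | significant, favours P-SUP | supportive | effective |
| not significant | significant, favours P-SUP | not supportive | effective |

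The third column does not change the fourth. This follows from the text and needs no arithmetic.

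**2. The plan's own sample size**

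Inputs from Sample size {14}: effect size 0.2, significance level 0.05, power 0.8, allocation 6:7, 2% death or withdrawal of consent, dropout 15% and 20%, total divisible by 13.

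- A two-sided t-test with these inputs needs 988, the smallest multiple of 13 that reaches 80% power. The stated 1001 is close to this.
- At 1001 the arms are 1001 × 6/13 = 462 and 1001 × 7/13 = 539.
- Analysed for hospital days: 462 × 0.98 × 0.85 = 385 and 539 × 0.98 × 0.80 = 423. Power is 0.81.

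The sample size is sound, and the point does not depend on it.

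**3. How easily the fallback can be met (illustration)**

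Assumptions not in the documents: no effect on hospital days; the two tests independent; the same true gain of 0.10 SD on each of the 11 self-reports; mean correlation r between them of 0.2, 0.3 or 0.5.

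With complete data, the between-group test of the ANOVA is a t-test on each participant's mean of the 11 z-scores.

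- SD of that mean = √((1 + 10r)/11) = 0.522, 0.603, 0.739.
- Non-centrality = (0.10/SD) × √(n₁n₂/(n₁+n₂)). For 385 v 423 this is 2.72, 2.35, 1.92.
- Probability of verdict by this route = power × 0.95, where 0.95 is the chance of a non-significant hospital-day test.

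| Analysed | r | Power of ANOVA in favour | × 0.95 |
|---|---|---|---|
| 385 v 423 | 0.2 | 0.775 | 0.74 |
| 385 v 423 | 0.3 | 0.652 | 0.62 |
| 385 v 423 | 0.5 | 0.484 | 0.46 |
| 453 v 528 | 0.2 | 0.848 | 0.81 |
| 453 v 528 | 0.3 | 0.735 | 0.70 |
| 453 v 528 | 0.5 | 0.560 | 0.53 |

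The second sample applies only the 2% loss (462 × 0.98 = 453; 539 × 0.98 = 528). It is arguably nearer the plan, because the 15% and 20% rates concern patients who must fetch hospital data from their insurer, whereas the section on missing data {20c} keeps everyone with a baseline questionnaire value and imputes missing end values. Neither row models that imputation.

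Sensitivity: with 385 v 423 and a gain of 0.05 SD, the last column becomes 0.26, 0.21, 0.15. With 385 v 423, the smallest observed mean difference that reaches significance is 0.072, 0.083 or 0.102 SD.

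**The case against.** The strongest reply is that the fallback is prespecified and openly argued, and that better physical health, less depression, anxiety and loneliness are worth having in themselves. The section says the pattern would indicate an effect of the intervention, not fewer hospital days, and the Objectives list all 11 variables as expected to improve. A randomised difference on them is a genuine finding. This stands, and it is why a fallback success should be reported. It does not rescue the unqualified word, because the section justifies the fallback by mediation and not by intrinsic benefit.

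Three stronger readings are tempting, and the documents do not support them.

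- *A null cross-lagged result would refute the causal chain.* It would not. The analysis is observational, and a non-significant path does not show that a link is absent. A positive path would not prove mediation of the treatment effect either. For the same reason the verdict should not be made to depend on it: no criterion for support across 11 variables exists, and if effects are late the analysis may miss them too.
- *The plan never looks at hospital days after month 18.* The primary change score ends there, while surveys run on to month 27. But the cross-lagged analysis uses hospital days for the intervals corresponding to the baseline and end surveys, and the interval belonging to the end survey is not defined. It could lie after month 18.
- *The 46 to 81% is a false-positive rate.* It is the power to detect an assumed real gain in self-reports, times 0.95. It says nothing about how often the link to hospital days fails.

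**Conclusion.** The point holds as a flaw in a decision rule that the article itself writes out, so it is not a detail left to an analysis plan. After a non-significant hospital-day test, a significant ANOVA on 11 unblinded self-reports is sufficient for the verdict. The rationale is assumed mediation with delay, and the analysis that examines that mediation has no stated role in the verdict. The same word can thus be earned with or without evidence for the primary hypothesis.

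The size is illustrative only. For an assumed 0.10 SD gain and mean correlation of 0.2 to 0.5, the fallback gives the verdict in about 46 to 74% of trials (385 v 423) or 53 to 81% (453 v 528) when hospital days do not change at all. The gain, the correlations and the independence of the two tests are assumptions. The gap in the rule depends on none of them.

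**What to change.** 1. **Reserve the unqualified verdict for the primary outcome.** In Statistical methods {20a}, state that P-SUP is judged effective only if the hospital-day test is significant in its favour.
2. **Fix the fallback wording in advance.** If only the ANOVA is significant in favour of P-SUP, the conclusion reads: P-SUP improves self-reported outcomes; a reduction in hospital days was not shown.
3. **State the role of the cross-lagged analysis.** Report it beside that conclusion as observational, supporting evidence that cannot upgrade the verdict, and define the hospital-day interval that belongs to each survey.

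The cost is wording, settled before outcome data are seen, with no new data or patient contact. The downside is that one favourable pattern no longer earns the unqualified word.

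A comparison of hospital days in months 18 to 27 is optional and exploratory only. Controls receive a shortened programme by then, and up to half the sample may be insured outside AOK RH and BARMER. With half of 453 v 528, about 226 v 264, power is about 0.60 for an effect of 0.2 and 0.20 for 0.1. A null result there would not settle whether an effect is merely late.
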